### Outcome measures

#### Emergency department

All older patients in the ED are regularly assessed with a geriatric screening ‘Geriatrisches Screening bei Klinikaufnahme’ (Supplementary file 1), which consists of six yes / no questions with a higher score predicting a poor outcome and the need for co-management or treatment by a geriatric team. Furthermore, all participants will be assessed for delirium using the Confusion Assessment Method (CAM) for Intermediate Care (CAM-IMC), which has shown better sensitivity and specificity in comparison to the widely used CAM for Intensive Care Unit (CAM-ICU) and includes the Richmond Agitation-Sedation Scale [34–36]. From the chart data chronic diseases and medication will be extracted to complement information given by the participant as soon as consent is provided. In addition, routinely drawn blood samples will be stored for further analyses of biomarkers.

#### Home assessment

After providing written consent to participate in the study, participants’ characteristics (age, sex, education, number and name of medications, pre-existing illnesses including joint replacements, smoking status, alcohol consumption, the use of hearing, seeing, and walking aids, and the living situation (e.g., alone, in a care facility) will be assessed. Additionally, the participants will be asked for detailed information on the recent fall that led to the visit at the ED, including time of the fall, location, and activity before falling, direction of the fall, and injuries. For a comprehensive geriatric assessment an extensive assessment battery will be used consisting of standardized, validated and widely used instruments. A detailed overview is given in Table 1.

**Table 1 Tab1:** Assessment battery during the home visits

Assessment tool	Outcomes	Timepoint
1. Participants’ characteristics (including personal and medical history)	Age, sex, education, pre-existing illnesses, usage of hearing, seeing and walking aids, living situation, smoking status, alcohol consumption, medication, joint replacements	T1
2. Specific fall history	Time of fall, location, activity before falling, direction of the fall, injuries	T1
3. German short falls efficacy scale (short FES-I) [37, 38]	Total score (ranging from 7 – 28)	T1, T2, T3, T4
4. Montreal Cognitive Assessment (MoCA) [39] a.MoCA memory index score (MoCA-MIS) [39, 40]	Total score (ranging from 0 – 30) Total score (ranging from 0 – 15)	T1, T2, T3, T4
5. Trail Making Test A and B (TMT A + B) [41]	Duration until completion in seconds & number of mistakes	T1, T2, T3, T4
6. (instrumental) activities of daily living: a.Lawton’s and Brody’s Index [42] b.Barthel Index [43] c.Jonkman Index [21]	Total score (ranging from 0 – 8) Total score (ranging from 0 – 100) Total score (ranging from 0 – 18)	T1, T2, T3, T4
7. Longitudinal Urban Cohort Ageing Study (LUCAS—FI) Functional Ability Index [44]	Functional ability classified in: Robust, postRobust, preFrail, Frail	T1, T2, T3, T4
8. Physical activity: a.German-Physical-Activity-Questionnaire 50 + (PAQ-50 +) [45] b.Physical Activity Scale for the Elderly (PASE) [46] c.Activity monitor (activPAL^©^) worn for 7 days	Energy expenditure per week Total score (ranging from 0 – 793) Number of steps, total active / inactive time	T1, T2, T3, T4
9. German Life Space Questionnaire (LSA-D) [47, 48]	Total score (ranging from 0 – 120)	T1, T2, T3, T4
10. Depressive Symptoms a.Depression in Old Age Scale (DIA-S) [49] b.Cornell Depression Scale [50]^a^	Total score (ranging from 0 – 10) Total score (ranging from 0 – 38)	T1, T2, T3, T4
11. Health-related quality of life EQ-5D – 3L + Scale [51, 52]	Total score (ranging from 0 – 15)	T1, T2, T3, T4
12. Functional performance: a.Hand grip strength test [53] b.Single leg stance test [54] ^b^ c.Short Physical Performance Battery Test (SPPB) [55]^b^	Grip strength measured in kg Duration in seconds Total score (ranging from 0 – 10)	T1, T2, T3, T4
13. Fall Calendar	Total number of falls during the follow up period	T2, T3, T4

^a^ The Cornell Depression Scale will be used instead of the DIA-S in case of severe cognitive impairment (MoCA < 18) or an existing diagnosis of dementia, ^b^ During the functional assessments, participants will be equipped with three wirelessly synchronized inertial measurement units (IMUs; Opal V1, Mobility Lab™ (ML), APDM, Inc., Portland, OR, USA), which will objectively assess postural sway and gait characteristics [56, 57]

#### Gait Laboratory (RCT for effect of perturbation protocol)

Participants will visit the gait laboratory ideally one week after their home assessments. The time between fall and visit to the gait laboratory will be documented. At the lab participants will be equipped with an activity monitor (activPAL^©^, PAL Technologies Ltd, Glasgow UK) and six wirelessly synchronized IMU’s (Opal V1, Mobility Lab™ (ML), APDM, Inc., Portland, OR, USA) to measure gait characteristics during all the assessments in the laboratory. A flow chart of the assessments, conducted in the gait laboratory, is provided in Fig. 2.

**Fig. 2 Fig2:**
[figure not shown]
Gait laboratory examinations including the randomized controlled trial

To determine overground walking speed, which will be used for all further assessments at the gait laboratory, participants will walk 3 m twice with the instruction to walk as fast as they can without running, then twice with the instruction to walk with their preferred walking speed. The mean time of the two trials under the same instructions will be taken and used to calculate maximal and preferred overground walking speed in km/h, respectively. To minimize the effect of starting, stopping or turning, 1 m will be added at each end of the walk way.

#### Reactive dynamic balance

Reactive dynamic balance will be assessed on the M-Gait treadmill (Motek Medical B.V., Amsterdam, the Netherlands), which enables anterior–posterior, medio-lateral and pitch perturbations. The integrated split-belt of the treadmill with separate force plates allows to perturb either both legs or just one leg during walking. The participants are secured using a safety harness.

Familiarization on the treadmill will start at 50% of the preferred overground walking speed. Treadmill walking speed will be gradually increased by 5% every 30 s until the participants will reach either 100% of the previously measured overground walking speed or an individually more preferable walking speed. Familiarization will last 6 min, which is regarded to be sufficient according to previous research [58–60]. The final minute of the familiarization will be used to analyze the participants’ gait at the preferred gait speed with the aforementioned sensors (activPAL^©^, APDMs). Additionally, three Microsoft Kinect Azure cameras (Microsoft, USA) will be used as a motion capture system [61].

After a two-minute break, participants randomized to the *no perturbation group* will walk twice for 4 min and 30 s with the individually determined treadmill walking speed. Participants will have a two-minute break between the two trials.

Participants randomized to the *perturbation group* will complete a perturbation protocol with similar duration and break time. The perturbation protocol will start with 30 s of the preferred treadmill walking speed, followed by 9 perturbations randomly presented to the participants. Time between perturbations will vary between 20–30 s, which is deemed a sufficient washout period [62]. Perturbations will be triggered through the integrated force plates at initial foot contact through custom application (D-Flow version 3.34.2, Motek Medical BV, Amsterdam, The Netherlands). Using the split belt option, each leg will be perturbed in anterior–posterior direction twice, mimicking slips and trips. Slips will be simulated by an acceleration of 3 m∙s^−2^ to a maximum of 180% of treadmill walking speed for 0.42 s. Trips will be provoked similarly with a deceleration of 3 m∙s^−2^ to a minimum of 40% of treadmill walking speed, which is in line with previous research [58, 59, 63, 64]. Besides these single leg perturbations, an emergency stop as in public transport will be imitated with both belts decelerating by 9 m∙s^−2^ for 0.12 s [58, 65]. Further, the protocol will include two contralateral sways, perturbing each leg once by a 5-cm platform translation in 3 m∙s^−2^ [58, 59]. A pitch of + and—5° respectively, with a duration of 1.0 s will imitate small slope changes as present on sidewalks or at bus stops. Gait adaptations to these perturbations will be measured throughout the trials, using the aforementioned systems.

#### Aerobic fitness

All participants will complete a treadmill test, assessing cardiorespiratory kinetics as an indicator of aerobic fitness [66]. Participants will be equipped with a face mask connected to a mobile system (MetaMax3B, Cortex Biophysik GmbH, Leipzig, Germany) to measure breath-by-breath gas exchange and will wear an ECG belt (CustoGuard belt 3, Customed, Ottobrunn, Germany) to assess beat-to-beat heart rate. The work rate protocol on the treadmill consists of two pseudo random binary sequences [67–69] which will change between 50 and 100% of the preferred gait speed, as assessed during familiarization on the treadmill. The protocol to assess aerobic fitness is shown in Fig. 3.

**Fig. 3 Fig3:**
[figure not shown]
Description of the work rate protocol, encompassing a warm up phase, two pseudo random binary sequences (PRBS) and a constant work rate phase on the treadmill

### Focus groups

In order to explore patients’ preferences, needs, facilitators and barriers of participating and adhering to falls prevention interventions and to support a patient centered intervention, focus group interviews will be established as part of the project [70]. 72 persons consisting of participants and caregivers will be recruited to join twelve focus groups (k = 6 with patients, k = 6 with caregivers).

Audio data from the focus group interviews will be transcribed verbatim with two multidisciplinary independent researchers analyzing the data. Content analysis according to Kuckartz will be applied with categories such as needs, preferences, barriers and facilitators deductively derived from the Theoretical Domains Framework [71]. Furthermore, categories can be derived inductively from the material recorded [72].

### Sensor data acquisition and machine learning

Normal and reactive individual gait patterns are recorded via both, the two activity sensor systems (Inertial Measurement Unit consisting of accelerometer, gyroscopes, and magnetometers—activPAL^©^, APDM) and the three front-facing depth cameras (Kinect Azure). The camera data are used to identify the spatial–temporal gait parameters and to label the perturbations and the associated reaction strategy. Based on this data, the individual reaction of a subject is identified using the IMU data of the two sensor systems (activPAL^©^, APDM).

Depending on the degree of homogeneity of the reaction pattern, either general / inter-individual classifiers (high degree of uniformity) can be trained or individual classifiers (high individual characteristics) can be constructed. The derived classifiers will be used to recognize slip, trip, and fall patterns over the time in IMU data during daily life.

### Safety

All serious adverse events / adverse events will be recorded on study specific adverse event forms. Overexertion during gait laboratory examinations will be avoided by using the preferred gait of the individual participant on the treadmill. Furthermore, breaks can be extended as needed and participants will be asked regularly if they feel fit to continue. If subjective or objective signs of fatigue or overexertion are seen, the protocol will be immediately interrupted. All adverse events will be reported to the principal investigator.

### Sample size

The recruitment goal of 450 older adults for the observational part of the study is the result of an analysis of the hospital data base of the Klinikum Oldenburg from the year 2018, which revealed a total of 1.182 patients, presenting to the ED without admission, aged between 60 and 103 years. These patients were registered within the symptom-groups ‘problem of the extremities’, ‘head trauma’ or ‘fall’. We assume that 48% of these patients are ineligible due to in- and exclusion criteria as published by Barker and colleagues and expect a further drop out of 38% due to not giving consent for study participation [73].

An independent biostatistician calculated the sample size for the embedded randomized controlled trial (RCT). Sample size calculation was performed via computer simulations based on the study of Pai and colleagues [22]. The level of significance was set as α = 0.05. As we aim for a power of 80% a sample size of at least *N* = 245 is required. According to previous research, a dropout of 17% may be expected in this subgroup, which led to the decision to aim for 300 participants [73].

### Statistical analysis

The endpoints will be compared between different home assessments: T1 (within 4 weeks), T2 (6 months), T3 (12 months), and the following yearly examinations after ED attendance. The association between multiple variables (e.g. age, time since recruitment etc.) and the trajectories of the different endpoints will be analyzed fitting a linear mixed model (LMM) / generalized linear mixed models, (GLMM, i. e. Logistic, Negative Binomial, Ordinal). For metric endpoints, we will check the normal distribution of the residuals in the corresponding LMM via Lilliefors-Test or descriptively via Skewness. We also plan to analyze stratified models (stratified e.g. by sex and / or initial physical fitness). Regarding the trajectories in the entire group, we will use the Friedman test for metric / ordinal data, if normal distribution of the residuals is not valid. The data obtained during the gait lab visit (gait analysis, aerobic capacity, physical activity) will be compared in a similar fashion. To identify simple predictors of declines in functional performance and physical activity as well as fall risks, that potentially can be obtained directly in the ED or at the general practitioner, regression analysis will be used. Setting parameters of the gait analysis and the cardiorespiratory fitness test as dependent variable and parameters of the home assessments as independent parameters, predictive factors for fall risks will be analyzed. Local significance level will be set to 5%. We will deal with missing value problems via complete Likelihood approach under the missing at random-assumption (MAR) in parametric models.

For the included RCT, we will analyze if a diagnostic perturbation session influences prospective fall risk. We will fit a logistic regression model, and will calculate p-values for coefficients plus estimates of the coefficients plus 95% confidence intervals.

Statistical analyses will be performed according to the ICH Guideline E9 ‘Statistical Principles for Clinical trials’ using validated statistical software (SAS, SPSS, R).

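### For whole-group trajectories, a normality check with no fixed criterion switches the analysis from the mixed model to a complete-case Friedman test, outside the plan's own missing-data approach

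*Protocol article*

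**What the plan says.** All the relevant text is in the Statistical analysis section of the protocol article.

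- **Main model.** "The association between multiple variables (e.g. age, time since recruitment etc.) and the trajectories of the different endpoints will be analyzed" with a linear mixed model or with "generalized linear mixed models, (GLMM, i. e. Logistic, Negative Binomial, Ordinal").
- **Check.** For metric endpoints, "we will check the normal distribution of the residuals in the corresponding LMM via Lilliefors-Test or descriptively via Skewness". No skewness value is given, and no rule for choosing between the two checks.
- **Fallback.** "Regarding the trajectories in the entire group, we will use the Friedman test for metric" and ordinal data, on a stated condition: "we will use the Friedman test for metric / ordinal data, if normal distribution of the residuals is not valid".
- **Missing data.** "We will deal with missing value problems via complete Likelihood approach under the missing at random-assumption (MAR) in parametric models". Nothing is said about missing visits under the Friedman test.

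Data assessment sets home visits at T1 (within four weeks of the ED visit) and at 6, 12 and 24 months (T2 to T4). The Discussion names loss during follow-up as a serious risk to the study.

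**The concern.** The fallback changes more than the distributional assumption. A likelihood mixed model uses every visit a participant attended and, if correctly specified, is valid when missingness depends on observed data. The standard Friedman test ranks visits within a participant, so anyone lacking one compared visit drops out of the analysis. It returns an omnibus p-value, with no slope and no estimated change, although the first part of the study exists to describe trajectories.

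At stake is the comparability of the whole-group results. Some endpoints would be analysed on everyone and others on completers only, and a check on the data would decide which. In an older cohort recruited after a fall, completers may differ from those who leave.

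**Working it through.** **1. Source of the dropout figure.** The Sample size section gives 17% dropout for the RCT subgroup and a requirement of 245. Then 245 / (1 − 0.17) = 295.2, so 296, which agrees with the stated target of 300. No dropout figure is given for the 450 in the observational part, so using 17% there is an assumption.

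**2. Complete blocks.** Participants retained = 450 × (1 − d), where d is the share missing at least one compared visit.

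| d | retained of 450 |
|---|---|
| 17% (borrowed) | 373.5, about 374 |
| 25% (assumed) | 337.5 |
| 30% (assumed) | 315 |
| 40% (assumed) | 270 |

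Intermittent misses count too. If each of T2 to T4 were missed independently by 5% or 10% (assumed), 450 × 0.95³ = 386 or 450 × 0.90³ = 328 would remain. The mixed model keeps everyone with at least one visit.

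**3. Bias in the estimated change.** Simulations used n = 450, four visits and a true mean change of −4.0 from T1 to T4. All parameters are assumptions.

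| dropout depends on | share lost | complete-case change | mixed-model change |
|---|---|---|---|
| previous level | 18% | −4.18 (realised −4.03) | −4.02 |
| previous decline | 17% | −3.43 | −4.00 |
| previous decline | 30% | −2.86 | −3.85 |

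In the first row complete cases slightly overstate the decline; in the other two they understate it. The sign and size therefore depend on the mechanism. The mixed model was closer to the truth in each setting.

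**4. How often the switch would occur.** Ten score distributions were assumed (the article gives none), with within-person correlation 0.7 and dropout rising to 17% by T4. This gives about 450 × (1 + 0.94 + 0.89 + 0.83) = 1,647 residuals. Rejection rates of the Lilliefors test at 5%, on marginal / conditional residuals:

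- FES-I-, DIA-S-, Lawton-, Barthel-, TMT- and PASE-like: 1.00 / 1.00
- SPPB-like: 1.00 / 0.97 (simulated on 0 to 12; Table 1 prints 0 to 10)
- MoCA-like: 1.00 / 0.53
- LSA-D-like: 0.33 / 0.13
- normal grip strength: 0.09 / 0.04

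That is 7 to 8 of 10 scales. With an assumed cut-off of absolute skewness above 1, only 1 to 2 of 10 would switch: TMT (1.70 / 1.19), and Barthel on marginal residuals only (−1.10 / −0.58). Both routes are open under the plan as worded.

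**5. Coherence of the rule.** The residual check is written for metric endpoints, yet the fallback also names ordinal data. For those the same paragraph already lists an ordinal mixed model, which does not need normal residuals.

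**The case against.** The strongest reply is that the fallback is narrow. It is confined to the visit comparison in the entire group, a question without covariates. Covariate associations, stratified models and predictor regressions are set out separately, nothing withdraws the mixed models from them, and the RCT's logistic regression is untouched. That stands. A reader might infer that the switch discards all covariate analyses; the text does not say so.

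Three further inferences are tempting and not supported.

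- **The switch will occur for most scales.** This holds only for the Lilliefors route and on assumed distributions. The plan also allows descriptive skewness, under which few scales might switch.
- **Only some 75 to 93 participants would form complete blocks.** The count follows if T4 is in the block and data collection ends in January 2024. With even recruitment, 3 of 15 to 4 of 16 recruitment months reach 24 months: 450 × 3/15 × 0.83 = 75 to 450 × 4/16 × 0.83 = 93. But this comes mainly from a separate conflict between the study dates in Study design, the recruitment period and the 24-month visit. The mixed model would also have few T4 values, the block is not defined, and the Discussion mentions possible extension through further funding.
- **Complete blocks bias the trajectory towards stability.** The first simulated mechanism moved the change the other way.

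It can also be said that a condensed article leaves detail to a fuller document. That does not answer the point: the switch itself, and the restriction of the missing-data method to parametric models, are stated here.

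**Conclusion.** The concern holds for the whole-group trajectory analysis, with moderate severity. Followed as written, the rule moves an endpoint from an analysis of all available visits under missing at random to a completers-only rank test without an estimate of change. The trigger leaves the choice of check and threshold open until the data are seen.

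At the borrowed 17%, about 76 of 450 participants (450 − 374) would leave the analysis of each endpoint that switches. How many endpoints switch cannot be determined from the article. Bias is possible, but neither its direction nor its size can be stated without knowing why people leave. It is not a defect that must block the study: the observational part names no primary trajectory endpoint, its 450 rests on recruitment feasibility rather than power, and the remedy needs no new data.

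**What to change.** Replace the fallback sentence before any outcome data are analysed.

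- Keep the linear or generalized linear mixed model, fitted to all available visits, as the whole-group trajectory analysis for every endpoint, and report the estimated change with its confidence interval.
- Where residuals are clearly non-normal, use the ordinal or negative binomial mixed model already listed, or keep the linear model with robust or participant-level bootstrap standard errors.
- Remove the Lilliefors or skewness result as a trigger. Residual plots can remain as a diagnostic.
- If the Friedman test is kept, label it a complete-case sensitivity analysis, state which visits form the block and report how many participants it uses.

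The cost is a few sentences and slightly more analysis work. The end of the study period and the 24-month visit should be reconciled separately, because they determine how much T4 data any method will have.

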To identify functional trajectories, a comprehensive geriatric assessment is needed, whose informative value can be improved by modern sensor technology. Further, an in-depth analysis of fall risk factors is mandatory. As dynamic reactive balance and aerobic fitness are not only discussed to be relevant fall risk factors but may also present treatment targets for future trials, they should be included in such an assessment battery. Dynamic balance dysfunctions are known to increase fall risk [7–9]. However, previous research indicates that even a single perturbation-based dynamic balance session influences functional trajectories and fall risk positively [22]. Therefore, observational studies using perturbation to assess dynamic balance have to control for potentially confounding effects of such a diagnostic session. The role of aerobic fitness as a risk factor is less clear and its association with static balance mostly based on cross-sectional findings [23, 24], making it a promising research target for longitudinal studies.

The worrying sequelae of falls for the individual but also their societal impact, call for action to strengthen and establish effective prevention programs, promoting high compliance of the participants [25]. Here, it is essential to take the populations’ specific needs into account. Patient-centered approaches have gained importance to identify potential barriers and facilitators to ensure adherence to such programs [26]. Therefore, exploring patients’ and their caregivers’ views on falls prevention seems crucial to build a realistic foundation for tailored intervention programs [27, 28].

The SeFallED study aims to identify long-term trajectories of older adults, presenting to the ED without hospital admission, after a sentinel fall. The study will combine geriatric assessments, sensor data and machine learning approaches. Further, the prognostic value of different, so far rarely studied risk factors such as aerobic fitness and dynamic reactive balance in predicting the trajectories, while controlling for potentially confounding effects of the respective risk factor assessments will be analyzed. Finally, these results will be combined with information on individual barriers, preferences and needs from the patients’ and caregivers’ perspectives to select and evolve adequate fall prevention programs in the future.

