The results of the SeFallED study will be used to identify risk factors with high predictive value for functional outcome after a sentinel fall. This will help to (1) establish a protocol adapted to the situation in the ED to identify patients at risk and (2) to initiate an appropriate care pathway, which will be developed based on the results of this study. (3) We will aim to select or (re)design existing interventions and / or develop effective interventions for older adults incorporating novel methods tailored to individual needs, barriers and preferences to lift fall prevention and individual compliance to a new level. (4) Automated falls detection based on machine learning algorithms may be integrated in devices used during daily life such as smart phones or wrist worn activity trackers, and will potentially play a major role in fall related research as well as for patient security in the future.

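### The only predictor regression given in detail has lab gait and fitness as its outcome, so as written it finds correlates of lab performance, not predictors of falls

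*Protocol article*

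**What the plan says.** All of this is in the protocol article.

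- **Statistical analysis, purpose.** Regression is planned with this goal: "To identify simple predictors of declines in functional performance and physical activity as well as fall risks". The predictors should be ones that an ED or a general practice could obtain.
- **Statistical analysis, specification.** The next sentence gives the model: "Setting parameters of the gait analysis and the cardiorespiratory fitness test as dependent variable and parameters of the home assessments as independent parameters". The predictor side and the claimed result are "parameters of the home assessments as independent parameters, predictive factors for fall risks will be analyzed".
- **Background, aim.** The study is to analyse "the prognostic value of different, so far rarely studied risk factors such as aerobic fitness and dynamic reactive balance in predicting the trajectories".
- **Discussion, use.** The results are meant to "identify risk factors with high predictive value for functional outcome after a sentinel fall", and so to support an ED protocol for finding patients at risk.
- **Home assessment, Table 1.** The fall calendar gives "Total number of falls during the follow up period" at T2, T3 and T4. Data assessment adds monthly telephone calls.
- **Statistical analysis, other models.** Trajectories of the endpoints are analysed by linear or generalised linear mixed models, with logistic, negative binomial and ordinal options. The RCT has its own logistic model for the effect of the perturbation session on prospective fall risk.

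**The concern.** A regression finds predictors of whatever stands on its left-hand side. Here that is laboratory gait and cardiorespiratory performance, while the stated conclusion concerns fall risk. The two coincide only if lab performance can stand in for fall risk, and this model cannot test that because falls are not in it.

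The direction also conflicts with the aim. The Background treats aerobic fitness as a possible cause or marker of later decline, whereas the specified model treats it as the result to be explained. An analysis plan that followed the sentence literally would report correlates of gait and fitness as fall predictors, and these could then be carried into an ED screening protocol. The question of whether fitness and balance predict the course after a fall would not be answered by this model.

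**Working it through.** **1. Roles side by side**

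| Variable | Aim (Background, Discussion) | Regression as specified |
|---|---|---|
| Falls | outcome of interest | absent |
| Decline in function or activity | outcome of interest | absent |
| Aerobic fitness | predictor | dependent variable |
| Reactive balance | predictor | not named; dependent variable if counted as gait analysis |
| Home-assessment measures | candidate simple predictors | independent variables |

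The reversal is exact for aerobic fitness. The Fig. 1 legend lists gait analysis and perturbation-based balance separately. Reactive balance is therefore either on the wrong side or missing; on neither reading is it a predictor.

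**2. Who can enter the model**

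The Statistical analysis section counts gait analysis and aerobic capacity as gait-laboratory data. Inputs are from Randomization and blinding and from Sample size.

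- Lab participants: 450 × 2/3 = 300.
- Check of the planned figure: 245 / (1 − 0.17) = 295.2, so 296, rounded up to 300. The target reproduces. The 245 comes from simulations whose event rates and effect size the article does not give, so it cannot be re-derived.
- Retained after 17% dropout: 300 × 0.83 = 249.
- With perturbation testing (1:1 allocation): 300 / 2 = 150. The other arm only walks (Reactive dynamic balance), so it has no perturbation responses.
- Standard errors scale with 1/√n. For a model limited to the perturbation arm, √(300/150) = 1.41, so intervals are about 41% wider than with all lab participants, other things equal.

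**3. Illustration of the consequence**

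The values here are assumptions, not figures from the protocol: n = 300, about one third of participants fall, 1,000 simulated studies, tests at 5%. Home measure H1 affects gait only (slope 0.4 residual SD per SD). Home measure H2 affects falls only (log-odds 0.5 per SD).

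| Model | H1 flagged | H2 flagged |
|---|---|---|
| Gait on H1 and H2 (as written) | 100% | 5.7% |
| Falls on H1 and H2 (logistic) | 4.7% | 96.8% |

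The model as written finds the true falls predictor at about the false-positive rate, and always flags the variable unrelated to falls. The scenario separates the two pathways completely, so it is an extreme case. It shows the logic and does not estimate the error in this trial. If gait carried part of the fall risk, the two models would agree more.

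**The case against.** The strongest case against the point has four parts.

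- **The preceding sentence has the right targets.** It names functional decline, activity decline and fall risk as what is to be predicted, from measures obtainable in the ED or general practice. The two sentences could describe two analyses. This stands in part: the text does not say that the second sentence specifies the first. But the second sentence makes its own claim about fall risk, and that claim does not follow from its model.
- **Falls may be modelled elsewhere.** A negative binomial mixed model suits calendar fall counts, and the choice of covariates can be left to an analysis plan. This stands as a limit on the point. It does not rescue a sentence that fixes the wrong outcome.
- **Home tests as proxies.** The Background discusses balance and fitness as fall risk factors, so finding cheap substitutes for lab measures is coherent and worth keeping. This stands, but under a different label from the one the protocol gives it.
- **The limit to 300.** Any analysis that uses lab variables has it. This stands: the limit is not a defect in itself. It matters only because the conclusion is meant for ED fallers in general, including those whom Participants and recruitment makes ineligible for the lab.

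**Conclusion.** The sentence is wrong as written, not merely brief. Its model has no fall or decline outcome, covers at most the planned 300 of 450 participants (67%), and gives aerobic fitness the opposite role to the study aim. The conclusion rests on the plain wording of the section and does not depend on the simulation.

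A reader might go further and infer that the study models falls nowhere, or cannot identify fall predictors at all. The article does not support that. The general mixed-model plan could take fall counts and could include lab measures as covariates, although neither is stated. The RCT model does use prospective fall risk, but for the effect of the perturbation session. The RCT comparison, the trajectory models and the data collection are unaffected.

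**What to change.** Reword the predictor paragraph in the Statistical analysis section:

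1. **Dependent variables.** Name prospective falls, from calendars and monthly calls, and decline in function and in physical activity. State the follow-up window; its length is the team's choice.
2. **All 450 participants.** Use ED and home-assessment measures as predictors. This is the model that bears on the ED protocol.
3. **Lab participants.** Add gait and cardiorespiratory parameters, and adjust for randomised perturbation allocation. The Background itself says that one perturbation session may change fall risk and has to be controlled for.
4. **Perturbation arm only (about 150).** Add reactive-balance parameters and acknowledge the lower precision. Everyone here has had the perturbation session, so results apply to people so exposed.
5. **Home-to-lab regression.** Keep it, labelled as a search for simple proxies of lab measures. Remove the claim that it yields fall predictors.

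The cost is one reworded paragraph and a few more models. All the variables are already collected. The main price is the smaller sample for reactive balance, which the design imposes in any case.
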